**Figure 1 figure1:**
[figure not shown]
Multiphase study flow of the OMNIdiasense project. AUROC: area under the receiver operating characteristic curve; BenCGM: Benefits of Continuous Glucose Monitoring Scale; BP: blood pressure; BurCGM: Burden of Continuous Glucose Monitoring Scale; CGM: continuous glucose monitoring; HbA1c: hemoglobin A1c; HIS: health information system; LFT: liver function test; MoH: Ministry of Health; NN: neural network; PAID: Problem Areas in Diabetes; PAQ-A: Physical Activity Questionnaire for Adolescents; RFT: renal function test; RSQ: Response to Stress Questionnaire;
SEDM: Self-Efficacy for Diabetes Management Scale; SQU: Sultan Qaboos University; SVM: support vector machine; T1DM: type 1 diabetes mellitus; TRIPOD+AI: Transparent Reporting of a Multivariable Prediction Model for Individual Prognosis or Diagnosis + Artificial Intelligence.

**Table 1 table1:** Description of the substudies by design, outcomes, and how each informs the next.

Substudy and aim	Design	Primary outputs/outcomes	How it informs the next phase
Substudy 1: characterize population	Retrospective cohort (Al Shifa records, n~1500)	Population characterization; pre/post HbA_1c_^a^, anthropometrics, BP^b^, lipids, RFT^c^, LFT^d^; sensor-wear days per week; baseline adherence prevalence	Provides the deidentified structured dataset (clinical + adherence label) used as the supervised-learning input for OMNIdiasense; defines candidate clinical predictors.
Substudy 2: identify correlates	Cross-sectional mixed methods (n=240 face-to-face interviews + qualitative open-ended responses)	Quantitative effect sizes for BenCGM^e^, BurCGM^f^, RSQ^g^, SEDM^h^, PAID-Peds^i^, PAQ-A^j^, and dietary screener on optimizer vs subuser status; qualitative themes on barriers and facilitators	Provides the psychosocial and behavioral feature set, the qualitative themes that inform MI content, and the effect sizes used to prioritize features for the AI model.
Substudy 3: AI tool development (7-step pipeline with validation hierarchy)	Prediction model development on combined substudy 1 + 2 dataset	OMNIdiasense risk score (probability of subuser status), with discrimination, calibration, and fairness metrics	The validated model becomes the assessment tool tested in the 2 evaluation arms below.

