### Substudy 1: Characteristics and Glycemic Outcomes of Omani Children Receiving CGMs

#### Design and Population

Substudy 1 is a retrospective cohort analysis of all Omani children with T1DM who received CGM through the national rollout between July 2024 and February 2025 across the 11 governorates. The minimum analytic exposure window is 3 months of CGM use from baseline.

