#### Expected Outcomes

Primary outcomes of substudy 1 are (1) the population-level prevalence of CGM optimizer status at ≥3 months and (2) the pre-post change in HbA_1c_. Secondary outcomes are pre-post changes in weight, BMI, BMI *z* score, systolic and diastolic blood pressure, lipid panel, renal function test (RFT), and liver function test (LFT); regional variation across governorates; and identification of routinely captured clinical predictors of optimal use that will be carried forward to the AI model in substudy 3.

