### Substudy 2: Correlates of CGM Adherence: Cross-Sectional Mixed Methods Study

#### Design and Population

Substudy 2 is a cross-sectional mixed methods study using supervised face-to-face interviews with adolescents aged 10-18 years drawn from substudy 1. RMs will randomly sample participants from the Al Shifa–derived cohort. The dependent variable, pattern of CGM use, will be dichotomized as CGM optimizers (≥6 days/week) and CGM subusers (<6 days/week or discontinued), consistent with prior pediatric work [25].

Eligible participants will include children aged 10-18 years with T1DM who received CGM under the national initiative and whose primary caregiver consents. Children will be excluded if they are unable to complete the structured interview owing to severe cognitive or sensory impairment.

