## Discussion

### Anticipated Principal Findings

We anticipate 3 principal findings. First, substudy 1 is expected to show that pediatric CGM uptake in Oman is high in the first 6 months of dispensing, but that a clinically important minority becomes subusers by month 3, with measurable variation across governorates. Second, substudy 2 is expected to confirm prior international findings that perceived benefit and burden of CGM, self-efficacy, and diabetes distress are the strongest psychosocial correlates of optimizer status, with additional Omani-specific contributors emerging from the open-ended responses. Third, substudy 3 is expected to show that OMNIdiasense, used as a decision-support adjunct followed by MI-guided behavioral sessions, is feasible to deliver, acceptable to families and clinicians, and produces a clinically meaningful between-group difference in adherence at 12 months that can power a future definitive trial.

These anticipated findings are framed as testable hypotheses, not foregone conclusions, and all statements throughout the abstract, manuscript, and conclusion have been rechecked to ensure that the strength of language matches the strength of inference that the proposed methodology can support.

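### Substudy 1 states its 3-month window as CGM use rather than time since dispensing; applied literally, this drops early discontinuers and raises the primary optimizer prevalence

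*Protocol article*

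**What the plan says.** Under Substudy 1, Design and Population, the cohort is "all Omani children with T1DM who received CGM through the national rollout between July 2024 and February 2025". The next sentence adds the analytic condition: "The minimum analytic exposure window is 3 months of CGM use from baseline".

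Under Substudy 1, Expected Outcomes, the first primary outcome is "the population-level prevalence of CGM optimizer status at ≥3 months"; the second is the pre-post change in HbA1c.

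Substudy 1, Data Collection, lists wear at two levels, at least 6 days a week or fewer than 6. It also lists the number of dispensations, but gives no rule linking that count to adherence status.

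Substudy 2, Design and Population, defines "CGM subusers (<6 days/week or discontinued), consistent with prior pediatric work", and the Abstract gives the same definition. The substudy 2 participants are "adolescents aged 10-18 years drawn from substudy 1".

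Table 1 says of substudy 1: "Provides the deidentified structured dataset (clinical + adherence label) used as the supervised-learning input for OMNIdiasense".

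**The concern.** The condition in the design section is on *use*, not on time since the device was dispensed. A child who stopped at week 4 does not accrue 3 months of use. If the sentence is applied as an entry rule, that child leaves the analysis, although the protocol counts a discontinued child as a subuser. The resulting prevalence would be conditional on persistence, which is part of what the outcome is meant to measure, and it would no longer describe all recipients.

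The timing matters because the Discussion expects that "a clinically important minority becomes subusers by month 3". Part of the group that the study expects to find could therefore arise inside the window and be removed by it.

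Three later uses depend on the same records. They supply the adherence label for OMNIdiasense, so clear examples of non-adherence could be missing from training; a held-out partition of the same data would not reveal this. They form the sampling frame for substudy 2. The 100 subusers of the single-arm pilot are in turn identified in substudy 2.

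**Working it through.** The article gives no sample size, precision target, expected prevalence or discontinuation rate for substudy 1, so there is no figure to reproduce. The check has two parts.

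**1. The wording side by side**

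- Favouring exclusion: the window sentence speaks of 3 months of use.
- Favouring elapsed time: the cohort sentence sets receipt of a CGM as the only criterion; the Abstract compares outcomes at baseline and at 3 months or later; the prevalence is defined at a time point; Data Collection takes treatment history at 3 months or more after CGM.
- Silent: no section says that early stoppers are excluded, and none says that they are kept and coded as subusers.

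**2. The size of the bias if they are excluded**

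Inputs:

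- N ≈ 1500 (Table 1).
- p = 0.50, the true optimizer share among all recipients. This is the planning value in Substudy 2, Sample Size, borrowed here because substudy 1 states none.
- d, the share of all recipients who stop before 3 months. Every value is an assumption.

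All early discontinuers are subusers, so leaving them out shrinks the denominator and does not change the number of optimizers:

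- observed prevalence = p/(1−d)
- bias = p/(1−d) − p = p·d/(1−d), which is positive for every d above 0

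With p = 0.50 there are 0.50 × 1500 = 750 optimizers:

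| d (assumed) | Children left out | Observed prevalence | Bias |
|---|---|---|---|
| 0% | 0 | 750/1500 = 50.0% | 0 |
| 5% | 75 | 750/1425 = 52.6% | +2.6 points |
| 10% | 150 | 750/1350 = 55.6% | +5.6 points |
| 20% | 300 | 750/1200 = 62.5% | +12.5 points |

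Sampling error for comparison: 1.96 × √(0.50 × 0.50/1500) = 0.025, or about 2.5 points. An assumed d of 5% would thus bias the estimate by about as much as its 95% half-width, and 10% by about twice that.

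The bias grows in proportion to p. At an assumed p of 0.70, d of 5%, 10% or 20% gives 73.7%, 77.8% or 87.5%, a bias of +3.7, +7.8 or +17.5 points.

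If discontinuers are kept and coded as fewer than 6 days a week, the bias is 0 for every d.

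**The case against.** The strongest reply is that the sentence means minimum follow-up. A window of 3 months from baseline can be read that way, and it would have a sensible purpose: extraction began in March 2025, when children given a sensor in January or February 2025 had not yet reached 3 months. Table 1 gives substudy 1 as about 1500, the same approximate number as all children who had received CGMs by February 2025, with no loss shown for non-persistence. Substudy 2 expects discontinued children in the frame drawn from substudy 1. This stands as a plausible reading, and it is why exclusion cannot be called certain. It does not settle the matter: the sentence still says use, and the discontinued children in substudy 2 could be only those who stopped after month 3.

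A reader might also infer that the absence of a discontinued level in the wear item itself removes children. The documents do not support that. A child who has stopped wears the sensor 0 days a week, which falls under fewer than 6, so the two listed levels are exhaustive. The extraction form (Multimedia Appendix 1) is also not shown and may record more than the article lists.

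Finally, a minimum period of exposure is a defensible choice for the pre-post HbA1c outcome. That is fair, but it does not justify the same condition for a prevalence in which stopping is one of the outcomes.

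**Conclusion.** The analysis population for a primary outcome of substudy 1 is stated in a way that conflicts, if taken literally, with the cohort of all recipients, the population-level prevalence and the subuser definition. Two readings are defensible and they give different denominators.

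The direction is certain if early discontinuers are excluded: prevalence can only be too high. The size is not known. With p = 50% and assumed early discontinuation of 0% to 20%, the bias runs from 0 to +12.5 points, against a half-width of about 2.5 points. Zero belongs in the range, because it is the result under the elapsed-time reading with discontinuers coded as subusers.

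A reader might go further and conclude that early stoppers are dropped, that the prevalence is overstated, and that the clearest non-adherent children are missing from the training data. The documents do not establish any of these; each follows only if the window sentence is applied as written. The point is therefore moderate, with medium confidence. It concerns substudy 1 and what is built on it, and does not touch the randomization or the definition of the primary outcome in substudy 3.

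**What to change.** In Substudy 1, Design and Population, define the window as at least 3 months elapsed since first CGM dispensing, regardless of continued use. State there that discontinued children count as subusers (fewer than 6 days a week), both in the prevalence denominator and in the label passed to OMNIdiasense. Add a rule for flagging discontinuation from the dispensation data already extracted, so that the regional pharmacists in the 11 governorates code such children alike. A separate discontinued level in the wear item would be useful detail, but the correction does not depend on it.

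The cost is a change of wording and one coding rule. Some of the records already compiled may need to be re-checked, and the reported prevalence may be less favourable. The Results section puts cleaning and pre-post analysis as still underway in April 2026 and feature engineering in the third quarter of 2026, so the change is easiest before the label reaches the model.

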#### Conceptual Background

T1DM in children is heterogeneous, and trajectories of glycemic control depend on age at onset, family history, comorbidities, and self-management capacity [11-13]. CGM has been shown to improve glycemic control in children when wear is consistent [14-16,19]. Quantifying baseline characteristics and short-term post-CGM outcomes in the Omani population will inform both clinical follow-up pathways and the variable set used to train OMNIdiasense.

#### Expected Outcomes

Primary outcomes of substudy 1 are (1) the population-level prevalence of CGM optimizer status at ≥3 months and (2) the pre-post change in HbA_1c_. Secondary outcomes are pre-post changes in weight, BMI, BMI *z* score, systolic and diastolic blood pressure, lipid panel, renal function test (RFT), and liver function test (LFT); regional variation across governorates; and identification of routinely captured clinical predictors of optimal use that will be carried forward to the AI model in substudy 3.

#### Data Collection

Regional pharmacists, supported by their RMs, will extract the following data from Al Shifa for each eligible child into a structured Google Form (Multimedia Appendix 1):

Demographic characteristicsMedical history of T1DMFamily history of diabetes (type and degree)ComorbiditiesDrug and treatment history (pre-CGM and ≥3 months post-CGM)Anthropometric measures (pre and post)Physiological measures, including blood pressure (pre and post)Laboratory investigations: lipid panel, RFT, LFT, HbA_1c_ (pre and post)CGM device type, cost, and number of dispensationsDuration of CGM wear (≥6 days/week vs <6 days/week)

#### Statistical Analysis

Descriptive statistics will be presented as frequencies, percentages, means, and SDs or medians and IQRs, as appropriate. Pre-post comparisons will use paired *t* tests or Wilcoxon signed-rank tests for continuous variables and McNemar tests for categorical variables. Differences across governorates will be evaluated with chi-square tests and ANOVA. Logistic regression will model predictors of optimal CGM use. Analyses will be performed in IBM SPSS Statistics (version 28) and R software (version 4.4; R Foundation for Statistical Computing). Reporting will follow STROBE (Strengthening the Reporting of Observational Studies in Epidemiology) guidelines (Multimedia Appendix 2).

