#### Data Analysis

Analyses will follow the intention-to-treat principle. Descriptive statistics will summarize baseline characteristics. Within-person change in the quasi-experimental arm will be analyzed with paired *t* tests, Wilcoxon signed-rank tests, or generalized estimating equations as appropriate. Between-group differences in the RCT will use *t* tests, chi-square tests, and mixed effects models with random intercepts for repeated measures. Multivariable linear and logistic regressions will explore predictors of adherence change. Missing data will be handled by multiple imputation under a missing-at-random assumption with sensitivity analyses. Prespecified subgroup analyses will examine age band (10-13 vs 14-18 years), sex, governorate (Muscat vs others), and insulin modality (multiple daily injections vs pump); any post hoc subgroup analyses will be flagged as exploratory. The pilot RCT report will follow the CONSORT (Consolidated Standards of Reporting Trials) 2025 extension for pilot and feasibility trials, and the interventional protocol adheres to SPIRIT (Standard Protocol Items: Recommendations for Interventional Trials)-AI 2025 (Multimedia Appendix 10).

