### Strengths and Limitations

Strengths of this protocol include national-scale recruitment across all 11 governorates, prospective alignment with SPIRIT 2025, CONSORT 2025, STROBE, COREQ, and TRIPOD+AI [45,48], the use of multiple validated psychosocial instruments, an explicit fairness and external-validation plan, and a coordinated research-management infrastructure that mirrors the operational structure of the MoH.

Anticipated limitations include reliance on routinely collected data with potential for missingness in substudy 1, possible social-desirability bias in face-to-face interviews in substudy 2, modest sample size in the pilot RCT, single-country generalizability, and the absence of patient and public involvement in initial design. The 12-month follow-up may be too short to detect changes in long-term complications, and the AI tool will require external validation in additional Gulf populations before scale-up. The pilot effect sizes will require confirmation in a definitive multisite trial, and the planned subgroup-fairness audit may itself be underpowered for rare strata.

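### Substudy 1's primary HbA1c change is tied to paired tests that, on observed records, describe only children with both values, not the rollout cohort

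*Protocol article*

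**What the plan says.** All references are to the Protocol article.

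- **Outcome.** Substudy 1, Expected Outcomes, lists two primary outcomes: the prevalence of optimizer status at 3 months or later, and the pre-post change in HbA1c.
- **Cohort.** Substudy 1, Design and Population, takes in "all Omani children with T1DM who received CGM through the national rollout between July 2024 and February 2025 across the 11 governorates". Table 1 puts this at about 1500. The same section adds: "The minimum analytic exposure window is 3 months of CGM use from baseline".
- **Data source.** Substudy 1, Data Collection, has pharmacists extract pre and post HbA1c from Al Shifa. No study visit secures the post value.
- **Method.** Substudy 1, Statistical Analysis: "Pre-post comparisons will use paired" t tests or Wilcoxon signed-rank tests for continuous variables, and McNemar tests for categorical ones. Nothing is said there about children who lack one of the two values.
- **Expected missingness.** Strengths and Limitations names "reliance on routinely collected data with potential for missingness in substudy 1".
- **Missing-data methods elsewhere.** AI model development has chained-equation imputation (m=20) with a tipping-point analysis. Substudy 3, Data Analysis, says: "Missing data will be handled by multiple imputation under a missing-at-random assumption with sensitivity analyses". Both stand under their own headings and neither is extended to the substudy 1 comparison.

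**The concern.** The population is every recipient, but the named tests, run on the data as recorded, work only on children with two recorded values. Whether a post value exists depends on attendance and on a clinician ordering the test, and either could be related to how HbA1c has moved. If so, the mean paired change answers a different question from the one the cohort definition poses.

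The article gives grounds for thinking such a relation possible. The Introduction cites real-world analyses in which adherence goes with HbA1c reduction, and Anticipated Principal Findings expects some children to have become subusers by month 3, which is when post values begin to count. That less engaged children are also tested less often is an inference; the article does not state it.

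With a cohort this size the confidence interval will be narrow, so selection could matter more than sampling error. The figure would probably be read as the result of the national programme. The secondary pre-post outcomes (weight, BMI, blood pressure, lipids, renal and liver tests) share the problem.

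**Working it through.** Substudy 1 states no power, missing share, expected change or SD, so there is no stated figure to reproduce. The only numerical input from the article is N of about 1500. Everything else below is an assumption, shown over a range.

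**1. The identity.** Let m be the share without a post value, d1 the mean change in children with both values, and d0 the mean change in the rest.

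- Cohort change = (1 − m) × d1 + m × d0
- Paired estimate = d1
- Bias = d1 − cohort change = m × (d1 − d0)

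The sign follows d1 − d0. The bias is zero if the two groups change equally.

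**2. Range.** With m from 0.10 to 0.40 and an absolute difference of 0.2 to 0.6 HbA1c points, the bias runs from 0.10 × 0.2 = 0.02 to 0.40 × 0.6 = 0.24 points, in either direction.

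**3. Example in which children without a post value improve less (d1 = −0.50).**

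| m | Cohort change if d0 = 0 | Overstatement | Cohort change if d0 = −0.25 | Overstatement |
|---|---|---|---|---|
| 10% | −0.45 | 0.05 (11%) | −0.475 | 0.025 (5%) |
| 20% | −0.40 | 0.10 (25%) | −0.45 | 0.05 (11%) |
| 30% | −0.35 | 0.15 (43%) | −0.425 | 0.075 (18%) |
| 40% | −0.30 | 0.20 (67%) | −0.40 | 0.10 (25%) |

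The paired analysis reports −0.50 in every row. Percentages are of the cohort change.

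**4. Against sampling error.** Assume an SD of change of 1.5, so SE = 1.5/√(1500 × (1 − m)).

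- m = 0.20: SE = 1.5/√1200 = 0.043. A bias of 0.10 is 0.10/0.043 = 2.3 SE, and a nominal 95% interval covers the cohort value about 36% of the time.
- m = 0.10 with the smallest difference: SE = 1.5/√1350 = 0.041. A bias of 0.02 is about half an SE, which is of little consequence.

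**5. Can a cohort estimate recover the value?** Take 50% optimizers changing by −0.8 and 50% subusers by −0.1, with a post value present in 90% and 60% respectively.

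- Cohort: 0.5 × (−0.8) + 0.5 × (−0.1) = −0.45
- Complete pairs: (0.45 × (−0.8) + 0.30 × (−0.1))/0.75 = −0.52
- Averaging the observed wear-specific changes over the whole cohort returns −0.45.

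A simulation of 500 runs with 1500 children gave −0.45, −0.52 and −0.45. The recovery holds because missingness was made random given wear status and wear was known for every child.

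**The case against.** **The tests are not complete-case by construction.** A reader might infer that naming a paired test rules out children with one value. It does not: the test can be run in each imputed dataset and pooled, and the statistical analysis plan, available on request but not shown, may say so. This stands. What remains is narrower. The article names the test for a primary outcome, expects missing data in this very substudy, and states imputation only under other headings; nothing in the section points to it here.

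**The target is not plainly every recipient.** The 3-month exposure window can be read as excluding children who stopped early, and they are natural candidates for little change without a post value. This stands too, and is a reason to state the population.

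**Overstatement is not shown.** A reader might also infer that the reported change will be too favourable. The article gives no missing share and no link between adherence and being tested. Clinics may test poorly controlled children more often, which could reverse the sign.

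**Imputation has limits of its own.** Wear comes from the same extraction and may be missing for the same children. It is also a post-baseline variable: as a fixed effect in a model for change it would give wear-specific changes unless these are averaged over the cohort.

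**Consequences are bounded.** The mean HbA1c change sets neither the substudy 3 sample size nor its primary outcome. What substudy 1 passes to the AI model is the adherence label and candidate predictors.

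**Conclusion.** The point holds in a conditional form. As described in the article, the primary HbA1c result of substudy 1 will apply to children with both values. It equals the cohort result only if having a post value is unrelated to the change. The departure is m × (d1 − d0): under the assumed ranges 0.02 to 0.24 HbA1c points, from about half a standard error to well beyond two. Overstatement is plausible if less engaged children are tested less, but the documents settle neither size nor direction, and they do not support saying that the national figure will be inflated. The change should be made; confidence is medium, because the full analysis plan is not shown and could already contain the imputation.

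**What to change.** 1. State whether children who stop CGM before 3 months belong to the HbA1c analysis, so that the population of the estimate is fixed.
2. Estimate the mean change for that population with the chained-equation imputation already planned for the AI data. Use wear category, number of dispensations, governorate, age, diabetes duration and baseline HbA1c as auxiliary variables in the imputation model, not as fixed effects in the model for change. An equivalent mixed model, averaged over the cohort, would also serve.
3. Report this beside the paired complete-pair result, which is kept.
4. Apply the tipping-point analysis already planned for the AI data, because missing-at-random cannot be checked.
5. Give the number and baseline profile of children without a post value.
6. The Results section says that pre-post analyses were underway as of April 2026. Date the change and label it as made after that work began.

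The cost is an analysis-plan amendment and some extra analysis; the auxiliary variables are already in the extraction or can be derived from it. The estimate then relies on missing-at-random, and the figure may be less favourable than the paired one.
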